### 2.10. Statistical Analyses

The normal distribution of the dataset will be assessed using the Shapiro–Wilk test. Analyses of variance (ANOVAs) with repeated measures will be used to analyze kinematic and kinetic parameters and pre-frontal cortex hemodynamic responses during gait initiation and during the steady state between the two interventions and time points. Significant interactions and main effects will be further examined using Bonferroni post hoc analysis. The significance level will be set at *p* < 0.05.

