### 2.3. Sample Size Calculation

The total sample size was estimated through an a priori power analysis, using the G power V 3.1.9.7 software (Heinrich-Heine-Universität, Düsseldorf, Germany). The following input parameters were applied using a repeated-measure ANOVA design: effect size f = 0.33, α = 0.05, power = 0.80, and correlation between repeated measures r = 0.50. The a priori power calculation revealed that the initial sample size required is 11. By considering a 10% dropout rate, 13 individuals with Parkinson’s disease will be recruited to voluntarily participate in this study.

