### 2.4. Experimental Design

A cross-over randomized control trial (RCT) will be adopted to investigate the acute effect of the MSK program for PD on anxiety, selected kinematic and kinetic parameters, and frontal cortex hemodynamic responses during gait initiation and during steady-state walking in people with PD, under the following conditions: (a) a synchronous learning format and (b) an asynchronous remote video-based format.

Volunteers will be asked to attend both conditions in a randomized order, separated by a washing-out period of at least one week. Levels of anxiety, kinematic, and DLPFC hemodynamic activity data will be collected before and after the two different interventions, which will last for approximately 45 min. The control situation will be defined based on the data collection at the same time points as above, but without any intervention following the 1-week washing out period. Ethical approval has been granted by Ethics Committee of University of Thessaly-Protocol number 2007. All procedures will be conducted in accordance with the declaration of Helsinki, in an appropriately equipped and safe laboratory, by qualified researchers with relevant experience. Research data are confidential and available to participants, who will be allowed to stop their participation at any time without previous notice.

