### 2.5. Randomization and Blinding

Participants will be randomly (randomizer.org) assigned by a leading researcher blinded to the study either to start with the synchronous intervention or with the asynchronous remote video-based intervention. Two evaluators also blinded to the scope of the study will take all measurements before and after interventions. It will not be possible to blind participants as the delivery of the class will reveal their allocation.

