### 2.7. Outcome Measures

Volunteers will attend both conditions (synchronous and asynchronous remote video-based) in a randomized order, separated by a washing-out period of at least a week. Kinematic, DLPFC hemodynamic activity and levels of anxiety data will be collected before (base-line data) and after the two interventions, while, on a third occasion, control data will be collected at the same time points but without any intervention.

Two experienced evaluators blinded to the group allocation will collect data. Baseline data collection will include: (1) Anthropometric characteristics (sex, age, body mass index), H&Y scale; (2) Anxiety Hamilton Rating Scale (Hamilton 1960); (3) Gait analysis using a 10-camera 3D motion analysis system (Vicon T-series, Oxford, UK) and two force platforms (Bertec 4060–10, OH) embedded in the laboratory floor; (4) Frontal cortex hemodynamic responses using f-NIRS (Portalite by Artinis NL); and (5) Unified Parkinson’s Disease Assessment Scale-III (UPDRS-III). Post intervention measurements will include: (1) Anxiety Hamilton Rating Scale (Hamilton 1960); (2) Gait analysis using a 10-camera 3D motion analysis system (Vicon T-series, Oxford, UK) and two force platforms (Bertec 4060–10, OH) embedded in the laboratory floor; (3) Frontal cortex hemodynamic responses using f-NIRS (Portalite by Artinis NL); and (4) Unified Parkinson’s Disease Assessment Scale-III (UPDRS-III).

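### The repeated-measures ANOVA treats the pre-session value as a time level instead of a covariate, which gives up precision on the format comparison, and it names no period term although format order is randomised

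*Protocol article*

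**What the plan says.** Section 2.10 fixes the method for the gait and hemodynamic outcomes: "Analyses of variance (ANOVAs) with repeated measures will be used to analyze kinematic and kinetic parameters", with the comparison made "during the steady state between the two interventions and time points". It continues: "Significant interactions and main effects will be further examined using Bonferroni post hoc analysis". The factors named are therefore intervention and time. No baseline covariate and no period or sequence factor is named.

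On the design, section 2.4 says "Volunteers will be asked to attend both conditions in a randomized order, separated by a washing-out period of at least one week", and that "data will be collected before and after the two different interventions, which will last for approximately 45 min". Section 2.5 randomises participants "either to start with the synchronous intervention or with the asynchronous remote video-based intervention". Section 2.7 adds that "on a third occasion, control data will be collected at the same time points but without any intervention". Section 2.3 assumes "correlation between repeated measures r = 0.50", with f = 0.33, alpha 0.05 and power 0.80, and arrives at 11 participants, or 13 after 10% dropout.

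**The concern.** With pre and post as two levels of time, the test of whether one format changes an outcome more than the other is the condition-by-time interaction. That test compares changes from the same-day baseline. Subtracting a baseline removes noise only when it is more closely related to that day's post value than to values from other days. If all values are equally correlated, as a single r implies, the subtraction adds noise. The pre value is already being collected and could be used as a covariate at no extra burden. With 11 to 13 participants, precision is scarce.

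The second element is order. The sequence of the two formats is randomised, yet the model has no term for first versus second session. The question is how much of any order effect would reach the contrasts that the plan tests.

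**Working it through.** **Reproducing the plan's figure.** The repeated-measures within-factor calculation uses lambda = f² × N × m / (1 − r), with m − 1 and (N − 1)(m − 1) degrees of freedom. With f = 0.33, r = 0.50, one group and m = 6 (three conditions × two times), it gives N = 11 with power 0.802. With m = 2, 3 or 4 it gives 21, 17 or 14. Inflating 11 for 10% dropout gives 11 / 0.9 = 12.2, so 13. The stated sample size therefore fits six measurements that share one correlation.

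**Variance of the format contrast.** Set the outcome variance to 1. Let rw be the correlation of pre and post in one session, and rb the correlation of values from different sessions.

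- Change-score contrast (interaction), per participant: 4(1 − rw).
- Post-value contrast adjusted for the session baseline: 2(1 − rb)(1 − rd²), where rd = (rw − rb)/(1 − rb).
- Ratio: 2/(1 + rd).

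With rw = rb = 0.50, rd = 0. The variances are 4 × 0.5 = 2.0 and 2 × 0.5 = 1.0. The ratio is 2.0 and the SE ratio 1.41. The factor of 2 comes from the equality of the correlations, not from the value 0.50.

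**Small-sample cost.** Estimating the baseline slope alongside a period term inflates the adjusted variance by about 1 + 1/(N − 4): 1.143 at N = 11 and 1.111 at N = 13. The ratios become 2/1.143 = 1.75 and 2/1.111 = 1.80. Simulation with near-balanced sequences agrees: 0.1801 against 0.1029 at N = 11 (1.75), and 0.1529 against 0.0846 at N = 13 (1.81). The SE ratios are about 1.32 and 1.34.

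**Sensitivity.** The article gives one r, so the same-day values below are assumptions. Between-day r is 0.5.

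| Same-day r | Ratio in theory | Ratio at N = 13 (theory / 1.111) |
|---|---|---|
| 0.5 | 2.00 | 1.80 |
| 0.7 | 1.43 | 1.29 |
| 0.8 | 1.25 | 1.13 |
| 0.9 | 1.11 | 1.00 |

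**Illustration.** For an assumed format difference of 0.66 SD, with all correlations at 0.50 and N = 13, power is 0.34 for the change-score contrast and 0.53 for the adjusted contrast with period. At N = 11 the figures are 0.29 and 0.44.

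**Order effects.** These were simulated with an assumed period effect of 0.5 SD.

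- Shift common to pre and post: the bias in the interaction is about zero, because the shift cancels in the change.
- Shift in the pre-post response on the second exposure: the bias is the shift times the sequence imbalance. For 7:6 this is 0.5 × 1/13 = 0.04; for 6:5, 0.5 × 1/11 = 0.05; for 8:3, 0.5 × 5/11 = 0.23. Simulated absolute values were 0.04, 0.05 and 0.22, and a period term removed the bias.

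**Control.** Sections 2.4, 2.5 and 2.7 read as placing control after the two randomised formats. If so, control and period 3 are the same column. With 13 participant effects, two condition terms and two period terms there are 17 columns of rank 16, so the model cannot separate control from order.

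**The case against.** The strongest reply is that a repeated-measures ANOVA is valid, matches the sample-size method, and contradicts nothing in the article, so preferring covariate adjustment is a matter of efficiency. That is correct, and it limits the weight of the point. A journal article may also leave period and sequence terms to a fuller plan, so their absence alone is weak evidence. What is not silence is the treatment of pre and post as levels of a time factor, which section 2.10 states.

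A second reply is that values about 45 minutes apart probably correlate more closely than values a week apart. This stands too: it moves the ratio down the table, to no gain at 0.9/0.5 with 13 participants.

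Three stronger readings are tempting and are not supported.

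- A reader might infer that the plan halves precision outright. That is the theoretical upper end, on the variance scale, under equal correlations.
- A reader might infer that order effects contaminate all the contrasts. A common session shift cancels in the interaction. It remains in the condition main effect, which section 2.10 also tests. The interaction is affected only if the response itself changes on repeat exposure, which is possible because section 3 says the class content is the same in both formats. A 9:4 split would leave (9 − 4)/13 = 38% of such a change in the contrast. However, the 27% chance of a split that bad or worse assumes simple randomisation, and section 2.5 does not say whether the list is balanced.
- A reader might infer that a period term would also protect the comparison with control. It cannot if control is always third.

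**Conclusion.** The point holds as a worthwhile improvement to a stated method, not as an error that invalidates the analysis. For the synchronous-versus-asynchronous contrast, the planned analysis has about 1.75 to 1.8 times the variance of a baseline-adjusted one at 11 to 13 participants. This rests on r = 0.50 applying equally to all measurements and on near-balanced sequences. If same-day correlation is clearly higher than between-day correlation, the advantage is modest or nil. The missing period term matters mainly for the condition main effect. It matters for the interaction only if response changes on repeat exposure, and then little when the sequences are near balance. Comparisons with control have a separate order problem that no analysis model can repair if control is always the third occasion.

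**What to change.** In section 2.10, replace the ANOVA with a linear mixed model for the post-session value. Include condition, the same-session pre value and the participant's mean pre value as fixed effects, a random participant effect, and small-sample degrees of freedom. For the format comparison, add period, defined as first or second active session.

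State where the control session falls. Do not use period to protect control comparisons unless control's position is also randomised. If control is always third, say that those comparisons are confounded with order.

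The model change is one of wording and needs no new patients, visits or measurements; randomising control's position would be a design change. The cost is a few degrees of freedom, with little or no gain if same-day correlation is very high. The period term is nearly free when sequences are balanced (simulated change-contrast variance 0.1801 to 0.1821 at 6:5) but dearer when they are not (0.1803 to 0.2300 at 8:3), so a balanced allocation list would keep that cost low.

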The aim of the proposed study is to examine the acute effects of a MSK program on select kinematic and kinetic parameters alongside DLPFC hemodynamics during gait initiation and steady-state walking in individuals with PD, performed in the following conditions: (a) a synchronous learning format and (b) an asynchronous remote video-based format. The program is customized for PD patients without deviating from the objectives of musicokinetic education. Primary outcomes will be the acute effects of a MSK protocol in people with PD on anxiety and locomotion. Secondary outcomes will be the effectiveness of an asynchronous remote video-based format for those patients that are not able to attend classes on site.

The novelty of the current design is the combined implementation of functional near-infrared spectroscopy (f-NIRS) in parallel with 3D gait analysis, which, until now, has yet to be evaluated in Parkinsonian patients following a MSK intervention. f-NIRS is extensively employed in chronic neurological disorders associated with aging, enabling direct measurements of the absolute concentrations of oxygenated and deoxygenated hemoglobin in the brain [16]. In relation to Parkinson’s disease, f-NIRS investigates the activity of the prefrontal cortex during tasks such as gait, postural stability, and dual-task performance, thereby determining motor vs. non-motor effects and executive dysfunction due to the disease’s pathology [16]. We shall non-invasively evaluate DLPFC hemodynamic activity in Brodmann area 46 during gait kinematics and kinetics evaluation using f-NIRS in order to investigate the cognitive involvement. Moreover, we argue that f-NIRS in conjunction with 3D gait analysis may provide valuable insights for understanding the mechanisms underlying the benefits of MSK program for PD.

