### 2.8. Primary Outcome Measures

Levels of anxiety will be evaluated via Hamilton Anxiety Rating Scale [17]. Ground reaction force (GRF) data captured at 1000 Hz for the right and left leg by the force platforms will be synchronized with the kinematic data obtained by the Vicon motion analysis system at 100 Hz. Twenty reflective markers will be placed bilaterally on the pelvis and lower extremities according to the marker set described in the literature [18,19]. The symmetrical center of rotation estimation (SCoRE) [20] and the symmetrical axes of rotation approach (SARA) [21] will be applied to estimate the hip joint center and the knee joint flexion axis, respectively.

For evaluation of DLPFC activation during gait, non-invasive measurements of local cortical hemoglobin (hBT) (i.e., blood volume), deoxyhemoglobin (HbH), and oxyhemoglobin (HbT) will be executed using a portable spectrometer (f-NIRS: PortaLite mini, Artinis Medical Systems, Zetten, Netherlands) with a capacity of light emission and detection of 840–760 nm, using a sampling frequency of 10 hz. The distance between NIRS optodes (i.e., sender and receiver) will be 25 mm, enabling a maximum penetration depth of 23 mm and an average measurement depth of 12.5 mm. Increased brain activity is generally considered to mirror increases in local HbO_2_ and decreases in HHb, resting on the mechanistic foundation of neurovascular coupling [22]. Decreased HbO_2_ responses can be considered a measure of neuronal suppression or altered hemodynamic re-distribution. The f-NIRS probe will be placed on the PFC of the right DLPFC [23]. To suppress any confounding influence of light, the probe shall be covered using black tape and a black cloth. For the collection, storage and visualization of f-NIRS data, the software application Oxysoft (Artinis Medical Systems, Zetten, The Netherlands) will be used. In addition to computing relative measurements of HBo2, HHb, and HbT using the modified Lambert Beer law, exportation of raw f-NIRS data will be performed and analyzed using a custom (MATLAB) script, used to inspect data for artifacts and processing.

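### The analysis in 2.10 gives no controlled test of the MSK effect and states no test for the primary anxiety outcome

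*Protocol article*

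**What the plan says.** **Question.** The Introduction states: "Primary outcomes will be the acute effects of a MSK protocol in people with PD on anxiety and locomotion". Section 3 repeats this. Both sections make the effectiveness of the remote format secondary, and 2.9 bases that on synchronous versus asynchronous delivery.

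**Outcomes.** The primary outcome measures in 2.8 begin with anxiety: "Levels of anxiety will be evaluated via Hamilton Anxiety Rating Scale". Gait and prefrontal measurements follow.

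**Conditions.** Each volunteer attends both formats in random order. Section 2.4 adds a third condition: "The control situation will be defined based on the data collection at the same time points as above", with no intervention given. Section 2.7 places these control data on a third occasion.

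**Analysis.** Section 2.10 names repeated-measures ANOVA for kinematic, kinetic and prefrontal hemodynamic data, "during gait initiation and during the steady state between the two interventions and time points", with Bonferroni post hoc tests. No other section gives an analysis for the control data or for anxiety.

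**Sample size.** Section 2.3 uses "effect size f = 0.33, α = 0.05, power = 0.80, and correlation between repeated measures r = 0.50" and arrives at 11, raised to 13 for dropout. It does not give the number of measurements or the effect tested.

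**The concern.** Section 2.10 lists both its outcomes and its comparison, and neither list matches the design. Sections 2.4 and 2.7 use the term for the two interventions in contrast to the control session, so on the article's own usage the ANOVA has two formats and two time points.

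That model offers two relevant effects. The format-by-time interaction asks whether the formats differ, which is the secondary question. The time main effect asks whether scores changed from before to after a session, with nothing to compare the change against. Section 3 expects the formats to be equally effective. If so, the interaction would show nothing and the evidence for MSK would rest on the time effect alone. Repeat testing, habituation to the laboratory or time since medication could produce the same change, and the control session was planned to separate such influences from MSK.

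For anxiety, one of the two stated primary outcomes, no test is given.

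**Working it through.** **1. Reproducing the planned sample size.** Inputs from 2.3: f = 0.33, α = 0.05, power 0.80, r = 0.50. Assumptions not in the document: one group, sphericity (ε = 1), and the usual G*Power within-factor form, with m measurements per person:

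λ = f² · N · m / (1 − r), df1 = m − 1, df2 = (N − 1)(m − 1).

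| Layout | m | N for 80% power | Power at 11 | Power at 13 |
|---|---|---|---|---|
| 3 conditions × 2 times | 6 | 11 | 0.802 | 0.879 |
| 2 formats × 2 times (as in 2.10) | 4 | 14 | 0.679 | 0.768 |

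For m = 6 and N = 11, λ = 0.1089 × 11 × 6 / 0.5 = 14.37 on 5 and 50 df, giving 0.802; N = 10 gives 0.751. For m = 4 and N = 11, λ = 9.58 on 3 and 30 df, giving 0.679. Dropout: 11 / 0.9 = 12.2, rounded up to 13, as stated.

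The stated 11 therefore fits six measurements, that is, three conditions including control. It does not fit the four in 2.10. This is an inference, because 2.3 does not state m.

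**2. False-positive rate of the time effect if read as an MSK effect.** Assumptions: MSK has no effect; every session drifts by δ (in SDs of a single measurement); r = 0.50 between all pairs of measurements.

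- Variance of one pre-post change: 2(1 − 0.5) = 1.
- Covariance of two changes from different sessions: r − r − r + r = 0.
- SD of the mean of the two MSK changes: √(1/2) = 0.707.
- Standardised drift: dz = δ / 0.707, tested by a two-sided one-sample t test on n − 1 df with noncentrality dz · √n.

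| Drift δ (assumed) | dz | Rejection, n = 13 | Rejection, n = 11 |
|---|---|---|---|
| 0.1 SD | 0.141 | 7.6% | 7.1% |
| 0.3 SD | 0.424 | 29.1% | 24.7% |
| 0.5 SD | 0.707 | 64.9% | 56.3% |

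The nominal rate is 5%.

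**3. Power of the controlled contrast.** Under the same correlation assumption, the mean of the two MSK changes minus the control change has variance 0.5 + 1 = 1.5, SD 1.225.

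| MSK effect (assumed) | dz | Power, n = 13 | Power, n = 11 | n for 80% power |
|---|---|---|---|---|
| 0.5 SD | 0.408 | 0.27 | 0.23 | about 50 |
| 0.8 SD | 0.653 | 0.58 | 0.50 | about 21 |

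**The case against.** The strongest reply is that 2.10 is loosely worded and the authors always meant to include the control session. The sample size supports this: 11 comes out with six measurements and not with four. That stands as evidence of intent. It does not repair 2.10; it adds 2.3 to the sections that 2.10 appears not to match. A reader might infer that the authors have decided to discard the control data. The documents do not support that; they support only a mismatch between sections.

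On anxiety, a journal article condenses, and a fuller plan may handle a clinician-rated scale by another method. A reader might infer that anxiety will go untested. The article does not say so, and this limb is weaker than the one on control. It remains because 2.10 does list its outcomes, and the first-named primary one is absent.

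A reader might also conclude that the stated ANOVA cannot test MSK at all. That goes too far: it does test a pre-post change in gait and hemodynamics. What it lacks is a comparison against control. Nor does the article say that the time effect will be interpreted as efficacy.

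The drift sizes have no source in the article, and at 0.1 SD the inflation is small. The contradiction between sections does not depend on them.

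Finally, the control contrast is not free of bias. Section 2.5 randomises only the order of the two formats. If control always comes last, MSK minus control also carries session order. This stands and limits what the remedy can achieve, but the contrast would still remove drift common to all sessions.

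**Conclusion.** The point holds: as written, 2.10 gives no controlled test of the primary MSK question and states no test for the Hamilton score, in conflict with the Introduction and with 2.4, 2.7 and 2.8.

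How much this could mislead depends on the unknown within-session drift, and the range in the working is illustrative. It assumes no MSK effect and equal correlations of 0.50, including between sessions at least a week apart. It concerns the outcomes that are in the ANOVA and says nothing about anxiety. That the sample size was based on six measurements is likely but not stated.

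**What to change.** Reconcile 2.10 with 2.3, 2.4 and 2.7:

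- Analyse condition (synchronous, asynchronous, control) by time for every primary outcome, and name the Hamilton score among them.
- State the primary contrast as the pre-to-post change under MSK, averaged over the two formats, minus the change under control. Make synchronous versus asynchronous secondary.
- State that the time main effect will not be read as an MSK effect.
- In 2.3, give the number of measurements and the effect tested, and restate power for the primary contrast at the planned 13.
- Report that the position of the control session was not randomised against the two formats, so the control contrast may include session-order effects.

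The measurements are already planned, so no data collection is added. The cost is more than wording, because the restated power may be well below 0.80. The authors would then have to justify a larger assumed effect, enlarge the sample, or present the MSK-versus-control result as an estimate with limited precision.

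### The primary outcomes are listed in two conflicting ways, and one 0.05 level with no rule across outcomes puts the chance of a false primary result well above 5%

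*Protocol article*

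**What the plan says.** Section 1 states: "Primary outcomes will be the acute effects of a MSK protocol in people with PD on anxiety and locomotion". Section 3 repeats this. Neither mentions haemodynamics among the primary outcomes.

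Section 2.8, headed as the primary outcome measures, covers three domains: the Hamilton score, force-platform and motion-capture gait data, and near-infrared spectroscopy of the dorsolateral prefrontal cortex. For the last it describes three signals ("In addition to computing relative measurements of HBo2, HHb, and HbT"). No variable is singled out.

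Section 2.10 assigns repeated-measures ANOVAs to the kinematic, kinetic and haemodynamic variables, in gait initiation and in steady-state walking, across two interventions and the time points. It names no test for the Hamilton score. One general sentence sets the level ("The significance level will be set at" p < 0.05). The multiplicity step is "Significant interactions and main effects will be further examined using Bonferroni post hoc analysis".

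Section 2.3 sizes the trial from "effect size f = 0.33, α = 0.05, power = 0.80, and correlation between repeated measures r = 0.50", and names neither an outcome nor a contrast. Section 2.7 adds a control occasion ("on a third occasion, control data will be collected at the same time points but without any intervention"), which the model in 2.10 does not mention.

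**The concern.** Two things go wrong together. First, a reader cannot tell whether the haemoglobin signals are confirmatory: 2.8 says they are, and sections 1 and 3 leave them out. Second, on either list there are several primary outcomes, each open to testing at the full 0.05, with no order and no adjustment between them. The Bonferroni step starts only once an ANOVA effect is significant and compares levels within that one variable, so it does not limit how many variables can give a false positive.

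At stake is what a positive primary result would mean. With 13 participants and several primary variables, one significant finding among many could be reported as the trial's primary success, and the protocol gives no basis for saying which finding was meant to count.

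**Working it through.** **1. The plan's own sample size.** Inputs from 2.3: f = 0.33, α = 0.05, power 0.80, r = 0.50. The number of repeated measures m is not stated. For one group and within-subject factors, λ = N·m·f²/(1 − r), df1 = m − 1, df2 = (N − 1)(m − 1).

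- With m = 6 (three occasions × two time points) and N = 11: λ = 11 × 6 × 0.1089 / 0.5 = 14.37, df 5 and 50, power 0.802. This reproduces "The a priori power calculation revealed that the initial sample size required is 11".
- With smaller m, 80% power needs N = 21 (m = 2), 17 (m = 3), 14 (m = 4) or 13 (m = 5). Of m = 2 to 6, only six measures give 11.
- Dropout: 11 / 0.90 = 12.2, rounded up to 13, as stated.

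The stated size therefore corresponds to one ANOVA at the full 0.05. No alpha was set aside for several primary outcomes.

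**2. Chance of at least one false positive, one independent test per outcome.** The formula is 1 − 0.95^K.

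| Set | K | Result |
|---|---|---|
| List in 2.8 without any gait variable: Hamilton + 3 signals × 2 phases | 1 + 6 = 7 | 1 − 0.95^7 = 30% |
| Same, without the Hamilton score, since 2.10 names no test for it | 6 | 1 − 0.95^6 = 26% |
| List in sections 1 and 3: Hamilton + 2 gait variables (assumed) × 2 phases | 1 + 4 = 5 | 1 − 0.95^5 = 23% |

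The number of gait variables is an assumption, because the article gives none. The first row counts none of them, so on that score it understates the list in 2.8.

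**3. Correlated outcomes.** Total haemoglobin is the sum of the other two signals, so independence is not realistic. Simulating seven equally correlated normal test statistics, each tested two-sided at 0.05, gives about 23% at correlation 0.5 and 18% at 0.7.

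**4. Main effects as well as the interaction.** Section 2.10 follows up both. If any of the three effects in a two-way ANOVA counted as success, seven outcomes would mean 21 tests: 1 − 0.95^21 = 66% if all were independent. The figures in steps 2 and 3 are therefore not upper bounds.

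**5. Power for a single named contrast.** Take a two-level contrast (m = 2) at the plan's own f = 0.33 and r = 0.50, assuming that these values carry over to it.

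- N = 11: λ = 11 × 2 × 0.1089 / 0.5 = 4.79, df 1 and 10, power 51%.
- N = 13: λ = 13 × 2 × 0.1089 / 0.5 = 5.66, df 1 and 12, power 59%.

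**The case against.** The best defence is that this is a condensed article. The exact gait variables, and any hierarchy or adjustment across outcomes, may stand in a full protocol or analysis plan that is not shown. That stands for the details: the missing list of gait variables is not criticised here. It does not answer the rest, because the article itself states the primary outcomes twice, differently, and itself states its significance level and its multiplicity step.

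A second defence is that six of the seven tests behind the 30% are haemoglobin signals, whose primary status is the very thing in dispute. That is fair, and it is why the narrower list is also computed. It still gives 23%, though only with assumed gait variables.

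Three stronger readings are tempting and are not supported:

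- A reader might infer that a false primary success is more probable than not. That needs either a large assumed number of gait variables (17 independent tests would give 1 − 0.95^17 = 58%) or a rule that any main effect, including a pure time effect, counts as primary success. The article states neither.
- A reader might infer that every primary variable has its own ANOVA. Section 2.10 gives none to the Hamilton score, which is reached only by the general sentence on significance.
- A reader might infer that the Bonferroni step is offered as control across outcomes. The text makes no such claim.

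**Conclusion.** The point holds. The contradiction between 2.8 and sections 1 and 3 needs no assumption. The lack of control across primary outcomes follows from 2.10 as written.

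The familywise error is several times the nominal 5%: 30% for seven independent tests, about 18–23% for the same seven at correlations of 0.7 to 0.5, and 23% for five independent tests on the narrower list. These figures assume one test per outcome and no true effects. The 23% for the narrower list also assumes two gait variables per phase. Counting main effects as success raises all of them. They illustrate the size of the inflation and do not estimate this trial's error rate exactly. The matter should be corrected, and it can be corrected without changing how the data are collected.

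**What to change.** 1. Make 2.8 agree with sections 1 and 3 by moving the haemoglobin signals to secondary or exploratory.
2. Name one primary outcome and one contrast, for example the change in Hamilton score under the musicokinetic programme versus the control occasion, tested at 0.05. Alternatively, apply Holm across a short, fixed list of primary outcomes.
3. In 2.10, name the Hamilton analysis and bring the control occasion into the model. A comparison with control cannot be made from a model that covers only the two interventions.
4. In 2.3, state the outcome and contrast and restate the power that the planned 13 participants give for it. This does not require enrolling more.

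The cost is more than wording. Fewer outcomes can be called confirmatory, the model in 2.10 changes, and the honest power figure may fall below the stated 80%. For a two-level contrast at the plan's own f and r it is about 51% with 11 participants and 59% with 13.
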